### Sleep quality

Sleep quality will be assessed through sleep questionnaires, estimation of hours of sleep, and polysomnography.
Sleep questionnaires: Two types of sleep questionnaire will be utilised during the study. The first, the RCSQ provides a score out of 50. The second (Little’s) involved a mixture of dichotomous questions and five-point rating questions [29, 30].Estimated hours of sleep: For both questionnaire responses, calculated outcomes will be compared between the treatment groups using Student’s *t* tests and supporting linear regression models to adjust for covariates.Polysomnography: In the subset of patients with polysomnography, the following will be analysed: total sleep time, sleep efficiency, percentage REM sleep, arousal index, and odds ratio product.

All calculated outcomes will be compared between the treatment groups using Student’s *t* tests and supporting linear regression models to adjust for covariates.

### ICU and hospital length of stay

Initial comparisons between the two groups for ICU and hospital length of stay will be compared using Student’s *t* test. Supporting analysis will also be carried out using Poisson regression, accounting for previously described covariates. Length of stay will be analysed in particular with the aforementioned subgroups.

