Based on the sample size calculations, with an alpha value of 0.05 and a power of 80%, a total of 850 patients have been recruited to the study, with 425 patients in each arm. Estimates of sample size were made based on the percentage of delirium-free assessments (the primary outcome) and, secondarily, the ICU LOS. LOS was chosen in addition to the percentage of delirium-free assessments as a significant relationship between delirium and LOS has been observed. Delirium assessment is by its nature subjective and the investigators wished to also allow the study to be powered to detect a reduction of LOS of 1 day (as an objective patient-orientated outcome). An audit of 100 patients across the two primary sites was used to provide preliminary data to guide sample size calculations where an average of 54% of assessments were deemed delirium free (standard deviation of ± 45%). The research group is interested in being able to detect a 10% increase in the percentage of delirium-free assessments. This would require a sample size calculation of 319 per group. Adjustment for non-parametric data (15%) increases this to 367 per group. It is expected that up to 10% of patients recruited in the study will not be assessable for delirium at any point during the study. To account for this, and missing data/loss to follow-up, the sample size was increased by 15% to 423 patients per group (total rounded to 850).

To detect a change in LOS of 1 day, using a sample size calculation for a gamma distribution, 387 patients per group would be required. The greater number of 850 was selected to have enough power to answer both questions. The formula used to calculate sample size was that described by Wand and Chow in 2007 [27].

The framework of the study is of superiority of melatonin over placebo for the prevention of delirium. Superiority analyses will be two-sided and considered statistically significant at the 5% level.

The DSMC is comprised of an independent intensivist, an epidemiologist, and a statistician independent of the trial statistician. The independent DSMC will review all serious adverse events and perform an interim analysis after 400 patients using the Haybittle-Peto stopping rule. The Haybittle-Peto stopping rule states that if an interim analysis shows a probability of equal to or less than 0.001 that a difference as extreme or more between the treatments is found, given that the null hypothesis is true, then the trial should be stopped early [28].

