### Duration of mechanical ventilation

The total number of hours of mechanical ventilation will be calculated for each participant. Comparison between the two groups will be made using Student’s *t* test. Supporting analysis will also be carried out using Poisson regression, accounting for covariates such as age, gender, admission type and diagnosis type.

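### The supporting Poisson models for length of stay and ventilator hours state no robust standard error or dispersion term; with the model-based error their intervals are too narrow, about 2-fold for ICU stay in days

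*SAP article*

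**What the plan says.** The section on ICU and hospital length of stay makes the t test the first comparison: "Initial comparisons between the two groups for ICU and hospital length of stay will be compared using Student’s" t test. The adjusted analysis follows: "Supporting analysis will also be carried out using Poisson regression, accounting for previously described covariates". No time unit is given for LOS.

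The section on duration of mechanical ventilation fixes the unit as hours: "The total number of hours of mechanical ventilation will be calculated for each participant". After a t test it again plans a Poisson model: "Supporting analysis will also be carried out using Poisson regression, accounting for covariates such as age, gender, admission type and diagnosis type".

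Neither section mentions overdispersion, a robust SE, or a quasi-Poisson, negative binomial or gamma model. Poisson regression is the only adjusted model named for these outcomes.

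The Study methods section gives LOS a different distribution: "To detect a change in LOS of 1 day, using a sample size calculation for a gamma distribution, 387 patients per group would be required". It reports neither the mean nor the shape used. The error rates are 5% two-sided and 80% power.

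**The concern.** LOS and ventilator hours are skewed durations, not counts of independent events. A Poisson model with its default SE takes the variance to be equal to the mean. Under the gamma distribution used to size LOS, the variance is proportional to the mean squared. The sizing and the adjusted analysis of the same outcome therefore rest on different variance assumptions.

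The dependence on units shows the problem without any assumed data. Recording the same stays in hours rather than days adds no information, yet it shrinks the model-based Poisson SE by sqrt(24). As the LOS unit is not stated, the width of the adjusted LOS interval is not determined by the plan.

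At stake is a supporting result that looks far more precise than it is. The SAP commits to 95% intervals and to P < 0.05 throughout. A non-significant t test could be printed beside a significant adjusted ratio solely because the adjusted SE is wrong.

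**Working it through.** **Inputs from the SAP article.** 387 per group for a 1-day change in LOS; two-sided 5% and 80% power, so Z = 1.960 + 0.842 = 2.802; 425 patients per arm; ventilation in hours. **Assumed, because not given:** the mean of ICU LOS, the mean and CV of hospital LOS, and the mean and CV of ventilator hours.

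**Step 1. The plan's own figure.** The 387 cannot be reproduced forwards without the mean and shape, so it is solved backwards in two ways.

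- Normal approximation, n = 2(SD × Z/δ)² with δ = 1 day: SD = sqrt(387/2)/2.802 = 4.97 days. Putting 4.97 back returns 387.
- Gamma log-ratio form, n = 2 × CV² × Z²/[ln(μ/(μ−1))]². For μ = 7: CV² = 387 × 0.1542²/(2 × 7.849) = 0.586, so CV = 0.765 and SD = 5.36 days. Over μ = 4 to 15 days the SD is 5.7 down to 5.1.

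Both routes put the implied SD at about 5 to 5.7 days.

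**Step 2. How much too narrow, in days.** Dispersion φ = variance/mean. True SE divided by model-based Poisson SE = sqrt(φ). Approximate type I error = 2[1 − Φ(1.96/sqrt(φ))].

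| Assumed mean (days) | Implied CV | φ | sqrt(φ) | sqrt(φ) with SD 4.97 | Type I error by formula |
|---|---|---|---|---|---|
| 5 | 1.108 | 6.14 | 2.48 | 2.22 | 43% |
| 7 | 0.765 | 4.10 | 2.03 | 1.88 | 33% |
| 10 | 0.523 | 2.74 | 1.65 | 1.57 | 24% |

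The last column uses the log-ratio φ. Over means of 4 to 15 days the factor runs from 2.9 down to 1.3.

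**Step 3. The unit.** Multiplying the data by 24 multiplies the variance by 576 and the mean by 24, so φ rises 24-fold and the factor by sqrt(24) = 4.9. For the three means above, the factors in hours are 12.1, 9.9 and 8.1.

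**Step 4. Simulation.** 3,000 null trials per scenario; gamma durations, 425 per arm, rounded to whole days or whole hours, two-group comparison without covariates.

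| Mean (days), CV | Poisson SE, days | Poisson SE, hours | Robust SE, days | Robust SE, hours |
|---|---|---|---|---|
| 5, 1.0 | 39% | 86% | 4.7% | 4.6% |
| 5, 0.9 | 33% | 83% | 5.3% | 5.2% |
| 7, 0.75 | 31% | 83% | 4.7% | 4.9% |
| 8, 0.62 | 26% | 81% | 5.5% | 5.5% |
| 10, 0.52 | 24% | 80% | 5.0% | 5.0% |

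Entries are type I error. The 39% lies below the 43% of Step 2 because the CV is 1.0 rather than 1.108. At mean 7 and CV 0.75, the mean model-based SE of the log ratio is 0.0259 in days and 0.0053 in hours; the robust SE is 0.0514 and 0.0513.

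**Step 5. Outcomes for which the article gives no figure.** Here φ = CV² × mean.

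- Ventilator hours, mean 48 to 150 h, CV 0.75 to 1.5: φ = 0.5625 × 48 = 27 up to 2.25 × 150 = 338, so the factor is 5.2 to 18.4.
- Hospital LOS in days, mean 15 to 20, CV 0.5 to 1.0: φ = 0.25 × 15 = 3.75 up to 1 × 20 = 20, so the factor is 1.9 to 4.5.

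**The case against.** **The SAP does not say the SEs will be model-based.** It says only Poisson regression. The abstract mentions additional files that are not shown, and an SE option might be set there. This limits the wording: robust errors are not stated, rather than ruled out, and every error rate above is conditional on the model-based SE. It does not remove the point. The article names a model whose default SE is wrong for these outcomes, while for the delirium severity models it does state an error structure (a random individual effect and a correlation structure).

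**The models are covariate-adjusted, and the figures use marginal dispersion.** This stands in part, since covariates would lower the residual dispersion. To bring φ to 1, however, they would have to explain 1 − 1/4.1 = 76% of the variance of ICU LOS at a mean of 7 days, and 1 − 1/27 = 96% for ventilator hours even at the lowest dispersion assumed.

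**The LOS mean is assumed.** True. At the low end the implied shape falls below 1 (0.81 at a mean of 5 days), which piles stays up near zero and fits poorly with the requirement of an expected stay of at least 72 h. The upper factor of 2.5 is therefore less secure than the middle of the range.

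**These are supporting analyses of secondary outcomes.** This stands fully and sets the severity. A reader might infer that the main LOS comparison is invalid, but the first comparison is a t test, which does not carry this defect. A reader might also infer that the costing is distorted. The Costing analysis section multiplies a reduction in LOS by a daily cost and uses neither a Poisson model nor an interval. Poisson point estimates also remain consistent when the mean model is right, whatever the variance.

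**Conclusion.** The point holds for the supporting adjusted analyses. As written, they pair a gamma-sized outcome, and a duration counted in hours, with a model whose default SE is too small and depends on the unit.

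The unit effect of 4.9 between days and hours is exact and needs no assumption about the data. For ICU LOS in days, the unit suggested by the 1-day target, the size is about 2-fold. That rests on the SD implied by 387 per group, an assumed mean of 5 to 10 days and model-based SEs. The 5 to 18-fold figure for ventilator hours and the figure for hospital LOS rest wholly on assumed means and CVs.

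A reader might conclude that all these intervals are several-fold too narrow. The documents do not support that for ICU LOS in days; it fits ventilator hours under the stated assumptions, and LOS only if it were counted in hours.

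The t tests, the primary outcome, the Poisson point estimates and the cost calculation are not affected. This should be fixed, but it does not threaten the trial's main conclusion.

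**What to change.** In the sections on length of stay and on duration of mechanical ventilation, specify robust (sandwich) SEs for the Poisson models, and state the time unit for LOS. That alone is enough: simulated type I error returns to about 5% in either unit.

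Alternatively, use a gamma model with log link for ICU and hospital LOS, which matches the sample size section, and a log-link model with robust SEs for ventilator hours. A gamma model does not suit ventilator hours if never-ventilated patients enter as zeros.

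The cost is a few words in the SAP and a different option or command in the analysis software. The intervals in these supporting analyses will be wider. According to the Trial status section, follow-up was still running and the data were still blinded, so the change could be made without knowledge of the results.

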### Duration of mechanical ventilation

The total number of hours of mechanical ventilation will be calculated for each participant. Comparison between the two groups will be made using Student’s *t* test. Supporting analysis will also be carried out using Poisson regression, accounting for covariates such as age, gender, admission type and diagnosis type.

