## Study methods

This is a multi-centre, randomised, double-blinded, placebo-controlled trial of melatonin versus placebo to decrease the rate of delirium in ICU. A total of 850 ICU patients have been randomised on a 1:1 ratio to receive either melatonin or a placebo. Study participants were administered an oral dose of melatonin 4 mg enterally or placebo once daily at 21:00hs. for up to 14 days or until discharge from the ICU. Participants were monitored twice daily for symptoms of delirium. Additionally, data is being collected on the duration and severity of delirium, sleep quality, hospital and ICU length of stay (LOS), duration of mechanical ventilation, and mortality.

Patients were randomised according to a computer-generated randomisation list, stratified by site, with standard block sizes of 6. Variable block sizes were considered unlikely to provide additional benefit, as the study drug and placebo have the same appearance and all clinical staff are blinded, thus maintaining allocation concealment. The randomisation list has been maintained by the University of Western Australia Centre for Applied Statistics.

The patients, investigators, ICU doctors, and nurses looking after patients enrolled in the study are blinded to the treatment that the patients are receiving. Only the University of Western Australia Centre for Applied Statistics, the compounding pharmacy, and the independent Data Safety Monitoring Committee (DSMC) (should they need to, in order to investigate an adverse event) have had access to the treatment allocation list.

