## Trial population

Screening data will be presented as descriptive statistics. Patients eligible to be considered for the study must be admitted to the ICU with an expected total LOS of at least 72 h, as determined by the treating intensivist. Eligible participants also must be able to be enrolled and treated within 48 h of being admitted to the ICU.

Exclusion criteria for participation in the study includes (1) patients aged < 18 years; (2) patients already on melatonin before their admission to ICU; (3) prior hypersensitivity reaction to any of the components of the study drug (melatonin, sucralose and glycerol, marshmallow flavour); (4) patients expected to be discharged within 72 h of their ICU admission; (5) expected/inevitable death within next 48 h; (6) pregnant or breastfeeding; (7) non-English speaking; (8) patients that are not expected to improve adequately to be able to be assessed with a CAM-ICU score during their ICU stay; (9) patients that are not able to be assessed due to neurological problems that would affect their ability to participate in a CAM-ICU assessment, as judged by treating physician; (10) no enteral route, as melatonin is not available in intravenous formulation; and (11) hepatic impairment defined as alanine transferase (ALT) > 500 IU/L, previous liver transplant, or liver cirrhosis categories Childs-Pugh B and C.

A CONSORT flow diagram will be presented. (Fig. 1) This will include the number of patients assessed for eligibility, excluded, randomised, allocated to each intervention arm, followed up, and analysed for each group. A report of withdrawals will be provided, describing the level at which they have occurred, the timing of withdrawals, and the reasons for the withdrawals.

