**Fig. 1 Fig1:**
[figure not shown]
Statistical analysis plan flowchart version 1

Baseline characteristics including age, gender, severity scores, source of admission, and diagnosis will be presented as a table and summarised.

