Finally, an analysis that looks at whether the individual reported a positive delirium assessment during their stay will be undertaken by comparing proportions between the groups through a logistic regression analysis controlling for variables including age, gender and length of stay.

The secondary outcomes to be analysed include (1) severity and duration of delirium, (2) sleep quality, (3) ICU and hospital length of stay;,(4) duration of mechanical ventilation, (5) mortality, and (6) economic analysis. Each secondary outcome will be adjusted for the same covariates as mentioned before: age, gender, delirium subtype, diagnostic category, and Pre-Deliric score.

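### Ventilation hours: the plan gives two different covariate lists, one of them open, and neither list nor the lead t test uses ventilation status at randomisation

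*SAP article*

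**What the plan says.** All references are to the SAP article.

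- **Duration of mechanical ventilation**, outcome: "The total number of hours of mechanical ventilation will be calculated for each participant".
- **Same section**, lead analysis: "Comparison between the two groups will be made using" Student's t test, with no covariates.
- **Same section**, supporting analysis: "Supporting analysis will also be carried out using Poisson regression, accounting for covariates such as age, gender, admission type and diagnosis type".
- **Analysis**, general rule, in the paragraph that lists ventilation duration as secondary outcome (4): "Each secondary outcome will be adjusted for the same covariates as mentioned before: age, gender, delirium subtype, diagnostic category, and Pre-Deliric score".
- **ICU and hospital length of stay**, for comparison: "Supporting analysis will also be carried out using Poisson regression, accounting for previously described covariates". The Mortality section refers back to the common list in the same way. The ventilation section does not.
- **Trial population**, enrolment window: "Eligible participants also must be able to be enrolled and treated within 48 h of being admitted to the ICU".
- **Study methods**, randomisation: "stratified by site, with standard block sizes of 6".
- **Baseline table** (text after Fig. 1): "Baseline characteristics including age, gender, severity scores, source of admission, and diagnosis will be presented as a table and summarised".

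Ventilation status at randomisation is not named as a covariate, stratification factor, subgroup or baseline variable.

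**The concern.** There are two linked weaknesses.

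First, the general rule and the ventilation section do not agree on what the supporting model adjusts for. The ventilation section adds admission type, which is in no other covariate list. It does not name delirium subtype or Pre-Deliric score, and its wording only gives examples. An analyst could defend several models after unblinding, and the plan's stated purpose is to rule that out.

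Second, patients may enter up to 48 h after ICU admission, so some will already be ventilated at randomisation. They can be expected to accumulate many more hours than the rest. Randomisation does not stratify on this status and no planned model names it. The predictable difference between the two kinds of patient therefore stays in the error term. A chance difference between arms in the share ventilated at entry also goes uncorrected.

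**Working it through.** **1. The two lists side by side**

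| Covariate | General rule (Analysis) | Ventilation section |
|---|---|---|
| Age | yes | yes |
| Gender | yes | yes |
| Diagnosis | diagnostic category | diagnosis type |
| Delirium subtype | yes | not named |
| Pre-Deliric score | yes | not named |
| Admission type | no | yes |
| Ventilated at randomisation | no | not named |
| Closed list? | yes | no |

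This part needs no assumption.

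**2. Inputs for the size of the loss**

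The article states no figure for ventilation hours, so there is nothing of the plan's own to reproduce. From the article: 425 patients per arm, two-sided 5% level. The 80% unadjusted power used below is a reference point only, because the trial was sized on delirium-free assessments and ICU length of stay.

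Assumed:
- share ventilated at randomisation, p: 40–80%
- hours in those patients: mean m of 96–120, SD s of 96–180
- 10% of the others ventilated later, with the same distribution of hours
- imbalance as under simple randomisation, ignoring any balance from site stratification

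**3. Formulas**

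- Mean gap between status groups: m − 0.1m = 0.9m
- Variance in the others: v0 = 0.1(s² + m²) − (0.1m)²
- Between-status variance: B = p(1 − p)(0.9m)²
- Within-status variance: W = p·s² + (1 − p)·v0
- R² = B/(B + W)
- Adjusted power = Φ(2.80/√(1 − R²) − 1.96)
- Standard error of the difference: √(2(B + W)/425) unadjusted, √(2W/425) adjusted

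**4. Central example: p = 0.6, m = s = 120 h**

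- Gap = 108 h; v0 = 0.1 × 28,800 − 144 = 2,736
- B = 0.24 × 108² = 2,799
- W = 0.6 × 14,400 + 0.4 × 2,736 = 9,734
- R² = 2,799/12,534 = 0.22; adjusted power 89%
- Unadjusted SE = √(2 × 12,534/425) = 7.7 h, 95% half-width about 15 h
- Adjusted SE = √(2 × 9,734/425) = 6.8 h, 95% half-width about 13 h

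**5. Ends of the assumed range**

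| p | m | s | B | W | R² | Adjusted power |
|---|---|---|---|---|---|---|
| 0.4 | 120 | 96 | 2,799 | 5,017 | 0.36 | 94% |
| 0.6 | 120 | 180 | 2,799 | 21,254 | 0.12 | 85% |
| 0.8 | 96 | 180 | 1,194 | 26,734 | 0.04 | 82% |

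A grid over the full assumed ranges has its minimum and maximum at the last and first rows.

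**6. Chance imbalance, central example**

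- 95% range of the difference in share ventilated: 1.96 × √(2 × 0.6 × 0.4/425) = 0.066
- Shift in the difference in mean hours: 0.066 × 108 = about 7 h, or 7.1/7.7 = 0.93 of the unadjusted SE

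**7. The supporting Poisson model**

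The article does not say which standard errors it will use. One null scenario was simulated (4,000 runs, 425 per arm): 70% ventilated at entry with mean 120 h, mean 24 h in the others. An unadjusted Poisson comparison with model-based standard errors rejected in about 87% of runs, and a comparison of means in about 5%. Adding a covariate alone would not cure that, which bears on the choice of model in the fix.

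**The case against.** The strongest reply is that nothing here is invalid. The t test holds its level over repeated randomisation, and its standard error already contains the variation from chance imbalance. In the central example the 7 h shift lies well inside the roughly ±15 h of the t test's own 95% interval. An unadjusted lead with adjusted support is the plan's usual pattern for continuous outcomes, and the lead analysis itself leaves no covariates to choose. All of this stands. It limits the point to efficiency, conditional imbalance and a loosely fixed supporting model.

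The sizes are also assumed throughout. R² is measured against a model with no covariates, so the gain over a model that already has age and diagnosis would be smaller to an unknown degree. That stands too.

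Four stronger readings are tempting, and the article does not support them:

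- **That imbalance biases the t test.** It does not on average. It only moves the estimate in a given sample.
- **That the total includes hours before randomisation.** The section gives no start of counting. The start is unspecified, and a fuller plan may define it.
- **That Pre-Deliric score and delirium subtype are dropped.** An open list fails to name them but does not exclude them.
- **That baseline status is already to hand.** The article says that duration of ventilation is collected, not that start and stop times are.

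What the reply does not remove is the mismatch: the general rule covers each secondary outcome, and the section for this one names something else.

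**Conclusion.** The point holds as a specification fault with a modest efficiency cost in one secondary outcome. That the two lists differ, and that one is open, is plain from the text. The precision loss has a clear direction but an uncertain size. Under the stated assumptions, baseline ventilation status explains about 4–36% of the variance, and 80% power would become about 82–94%. The gain is under 2 percentage points at the low end (80% ventilated, mean 96 h, SD 180 h). It does not touch the primary outcome or the validity of the planned t test.

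**What to change.** In the section on duration of mechanical ventilation:

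1. Replace the open-ended covariate wording with one closed list: Pre-Deliric score, diagnostic category, delirium subtype, age and gender (the general rule), plus ventilated at randomisation (yes/no). Adding the last depends on the sponsor confirming that it can be derived from recorded data.
2. Make the lead estimate a linear regression of hours on treatment and that list, with robust standard errors. It takes the place of the supporting Poisson model.
3. Keep the t test as the unadjusted supporting analysis.
4. State that hours are counted from randomisation, if start times are recorded.

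Cost: a change of wording, to be made before unblinding, one derived variable, and an adjusted rather than raw lead estimate. Enrolment is complete, so if status at randomisation was not captured it would have to be retrieved. In that case the closed list without it still resolves the contradiction.
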